### 3.3 Pre-planned secondary analyses:

- Risk adjustment for preoperative surgical risk (RACHS and Aristotle)
- Health care costs
- Subgroup analysis for age (<28d, <42d, <90d), and univentricular or biventricular hearts
- Number and duration of postoperative organ dysfunction (assessed by respiratory, cardiovascular, renal support)

- Postoperative renal failure, maximum creatinine, need and duration of renal replacement (CVVHF, CVVHDF, peritoneal dialysis, SCUF if on ECLS postoperatively), and blood, serum and urine markers of renal dysfunction including secretory/concentration capacity
- Volume and type of fluid and of transfusions given during CPB, and during the first 24 and 48 hours post CPB in PICU.
- To compare treatment response between patients depending on pre-intervention severity assessed by markers of inflammation and organ failure
- To biochemically define responders to the intervention using markers of inflammation
- Impact of open chest
- To investigate predictors of worse outcome including transcriptomic analyses, biomarkers, and clinical factors
- To investigate the association of hyperoxia with outcomes
- Subgroup analyses on infants and children undergoing several CPB procedures during first years of life, including neurocognitive and functional outcome
- Neurodevelopmental and functional follow-up
- Incidence and severity of postoperative delirium (using sedation and delirium scoring)
- Relationship of postoperative delirium and neurodevelopmental outcomes to intervention and inflammation

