### 7.3 Blood Sample Collection for Inflammation analysis

**Biomarker Analysis and Biobanking:** Blood markers for myocardial injury and inflammatory response will be collected on induction of anaesthetics (baseline – pre bypass), at admission to PICU (0 hours – post bypass) and at 12, and 24 hours for the following purposes: i) to test the impact of the intervention on markers of inflammation; ii) to stratify patients in to high- versus low inflammatory groups; iii) to biochemically define responders to the intervention (to identify patient subgroups that are more likely to respond to a specific treatment), iv) to develop improved markers of outcome post cardiac surgery. Collection of blood for biomarker analysis and biobanking is optional and parents will be asked to provide their permission during the consenting process.

**Blood sampling and processing.** *Preoperative baseline* (before onset of cardiac surgery, done by anaesthetist during the induction of the patient once the arterial line has been inserted): 1-2ml of EDTA blood (for DNA), 2.5ml of blood (PAXgene tube for gene expression markers), 1-2ml of serum *Postoperative at 0,12,24 hrs* (in PICU until discharge to the ward): 2.5ml of blood (PAXgene tube - time point 0 only), 1-2ml of serum. The total amount of blood taken is 10-15ml for the entire study duration, which is much less than the amount of blood taken for routine perioperative care tests. The samples will be processed within 30 minutes, centrifuged, aliquotted and immediately frozen. The samples will be kept in a security protected freezer in the each institution, and will be transferred in batch every 12 months to the Centre for Children's Health Research, Brisbane, Australia. Urinary electrolytes and NH4 will be measured from patient urine collected through the

standard IDC at baseline, admission to PICU, and 6-24hours to assess for renal concentration and secretory function. Paired arterial and venous gases will be collected postoperatively at 0,6,12,24,48 hrs (in PICU until discharge to the ward or removal of arterial line, whichever occurs first) to assess for lactate and SaO2-SvO2 gradient. Each arterial or venous blood gas sample requires 0.2mls of blood and would total 2mls across all samples. Routine paired gases are often part of standard clinical care.

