***Gene and gene-expression based markers:*** gene changes and gene-expression will be investigated, to test the individual response to the intervention, and to develop improved markers. Gene-expression analyses will be performed on RNA aliquots obtained from the PAXgene Blood RNA tubesRNA will be extracted using PAXgene silica-membrane technology (PAXgene Blood miRNA Kit) on QIAcube extractor at TRI-UQ. Full transcriptome sequencing will be done at the Institute for Molecular Biosciences Sequencing Facility at University of Queensland. Raw Illumina reads will be mapped to the human reference genome. HTSeq-count will be used to count reads mapping to exons, and to estimate fragments mapping per kilobase per million mapped reads (FPKM). A generalised linear model framework in EdgeR will be used to identify differentially expressed genes between disease groups, considering genes with a false-discovery rate (FDR), as estimated by a Benjamini-Hochberg procedure, to be differentially expressed. We will use Fisher's exact test to calculate whether particular Gene Ontology categories or KEGG pathways are significantly enriched

in differentially expressed genes. We will use the weighted gene coexpression network analysis (WGCNA) tool, to identify co-regulated gene modules, and identify differentially expressed modules by association of module 'eigengene' with disease group. We will *derive minimal signatures distinguishing the disease groups* using a rapid forward-selection algorithm we have previously used. The performance of the signatures will be assessed using cross-validation.

**Determination of serum vitamin C levels and their relationship with presence and severity of response to CPB.** The unique dataset and biobank acquired thanks to this study will enable to improve our understanding of response to CPB in children. Specifically, we will investigate whether levels of vitamin C in blood are associated with severity after CPB, as postulated by recent studies who have proposed ascorbic acid as a novel treatment. These tests will be performed in batch in Queensland Health and University of Queensland laboratories. Test results will be available to researchers only and will not affect clinical care as performed in batch for research only purpose. The tests will be done on already available study aliquots and will not increase or alter the amount of study blood taken.

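### The gene-expression work is meant partly to test response to NO, but every gene analysis written contrasts undefined disease groups without randomised arm, so it cannot separate effect modifiers from prognostic genes

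*Combined protocol and SAP*

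**What the plan says.** In the protocol's section on the use of biobanked blood (7.3), the gene-expression paragraph opens with its purposes: "gene changes and gene-expression will be investigated, to test the individual response to the intervention, and to develop improved markers". The opening of section 7.3 gives as purpose (iii) of the blood sampling "to biochemically define responders to the intervention (to identify patient subgroups that are more likely to respond to a specific treatment". Section 3.3 lists among the pre-planned secondary analyses "To biochemically define responders to the intervention using markers of inflammation".

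The methods for genes then follow in one chain:

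- Gene level: "A generalised linear model framework in EdgeR will be used to identify differentially expressed genes between disease groups", with selection described as "considering genes with a false-discovery rate (FDR), as estimated by a Benjamini-Hochberg procedure, to be differentially expressed". No cut-off is stated.
- Pathway level: enrichment tests on the genes so selected.
- Module level: "association of module 'eigengene' with disease group".
- Signature level: "derive minimal signatures distinguishing the disease groups", assessed by cross-validation.

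'Disease group' is not defined. No step names randomised arm or a gene-by-arm term. RNA is collected before bypass and once more at PICU admission, after NO exposure. Sampling for biomarkers is optional.

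**The concern.** Asking which children are more likely to respond is a question of effect modification. Its null hypothesis is that the effect of NO does not vary with the marker. A contrast of expression between groups of children, pooled over arms, has a different null: that expression is unrelated to group membership. In a parallel-group trial no child's own response is observed. A child who does well on NO cannot be told from one who would have done well without it, unless the marker's relation to outcome is compared between the arms.

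The stated response aim therefore has no analysis that answers it. If the disease-group list were used to answer it, genes that merely predict outcome would stand beside genes that change the effect of NO, with nothing in the output to separate them.

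**Working it through.** **1. Is there a matching analysis elsewhere?**

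| Place | What it offers | Marker-by-arm model? |
|---|---|---|
| Protocol 7.3, gene expression | Disease-group contrasts at gene, pathway, module and signature level | No |
| Protocol 7.3, cytokines and metabolites | Separates children with worse outcomes, including LCOS, from the others | No |
| Protocol 3.3 | Treatment response by pre-intervention inflammation and organ-failure markers | Aim only; no model, genes not named |
| Protocol 3.3 | Transcriptomics, listed under prediction of poor outcome | No (prognostic) |
| SAP, subgroup analyses | Interaction terms | Age group and physiology only |
| SAP, analysis principles | Inflammatory markers left to separate reports | No; transcriptomics not mentioned |

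**2. Does any reading of 'disease groups' supply the interaction?** Outcome groups give a prognostic test. Lesion types or high- versus low-inflammatory groups are further from response. Even if the groups were the arms, the test would be of NO's effect on expression, not of who benefits. None is a gene-by-arm interaction.

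**3. Size.** The documents give no sample size, effect size or cut-off for this work, so there is no figure to reproduce. The simulations below take disease group to mean LCOS yes/no. They compare a two-sample test of mean expression by LCOS status, standing in for the edgeR contrast, with the Wald test of the expression-by-arm term in a logistic model. Expression is N(0,1) and allocation 1:1.

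*Setting A* (all inputs assumed): 25% LCOS, NO log-odds effect −0.5, N = 300/600/1000, two-sided 5% per gene. Small ranges reflect repeated runs.

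| Gene | Disease-group test | Interaction test |
|---|---|---|
| Prognostic, OR 1.5 per SD, no interaction | 84–85 / 98 / 100% | 3–6% |
| Prognostic, OR 1.3 per SD, no interaction | 46–49 / 78–79 / 92–95% | about 5% |
| Interaction OR 2.0, acts in NO arm only | 60 / 90 / 98% | 72 / 93 / 99.6% |
| Interaction OR 2.0, acts in control arm only | 78–80 / 96–97 / 99.8–100% | 69 / 93 / 99.5% |
| Interaction OR 2.0, exact crossover | 5–7 / 6–8 / 8% | 73 / 94–95 / 100% |

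*Setting B*: LCOS 35.8% control and 12.3% NO (pilot, protocol Table 1) or 30% in both arms (assumed); log-OR 0.5 per SD; N = 600/1320; 5% per gene.

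| Gene | Pilot rates: disease-group | Pilot rates: interaction | Equal 30%: disease-group | Equal 30%: interaction |
|---|---|---|---|---|
| Prognostic | 99.6 / 100% | 5.1 / 4.7% | 100 / 100% | 3.8 / 4.4% |
| NO arm only | 38 / 64% | 64 / 93% | 78 / 99% | 79 / 98% |
| Control arm only | 88 / 99.6% | 67 / 94% | 79 / 98% | 80 / 99% |
| Crossover | 32 / 62% | 99.7 / 100% | 4.5 / 3.9% | 100 / 100% |

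**4. Why the pattern arises.** To first order, the pooled covariance between expression and LCOS is ½[b_c·p_c(1−p_c) + b_t·p_t(1−p_t)], where b is the slope and p the LCOS rate in each arm. At the pilot rates, p(1−p) is 0.358×0.642 = 0.230 in control and 0.123×0.877 = 0.108 on NO.

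- Prognostic: ½×0.5×(0.230+0.108) = 0.085
- Control arm only: ½×0.5×0.230 = 0.058
- NO arm only: ½×0.5×0.108 = 0.027
- Crossover: ½×0.5×(0.230−0.108) = 0.031

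All four are non-zero, so the pooled test sees something in each and cannot say which it is. With equal rates the crossover terms cancel exactly.

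**5. A stricter threshold.** At 0.001 per gene and the pilot rates (N = 600/1320), the prognostic gene is still flagged in 93/100% of runs by the disease-group test and in at most 0.1% by the interaction test. The interaction test finds an NO-arm-only modifier in 16/55%.

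**The case against.** The strongest reply is that the contrast is right for what it does. One of the two purposes in the gene-expression paragraph is better markers, section 3.3 places transcriptomics under prediction of poor outcome, and a disease-group comparison serves both. That stands. On the test's own null, detecting a prognostic gene is correct detection; it becomes an error only if the list is used for the response aim.

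A reader might infer that the plan will report prognostic genes as response markers. The documents do not say so: they call the genes differentially expressed and tie the signatures to disease groups.

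A reader might also infer that the written test misses true effect modifiers. That is too strong. Modifiers acting in one arm were flagged in 60 to 100% of runs in Setting A. In Setting B the NO-arm-only modifier was flagged in 38 to 64% at pilot rates. Only a crossover modifier is reliably missed, and only when LCOS rates are similar between arms.

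Two further points stand. Reading disease group as LCOS is an assumption, though it agrees with the neighbouring cytokine and metabolite paragraph; under another reading the rejection rates do not apply. And section 3.3 does pre-plan a comparison of treatment response by pre-intervention inflammatory markers, but it gives no model and does not name genes. None of this supplies a method for the response aim stated for gene expression.

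**Conclusion.** The point holds in this form: protocol 7.3 states a response aim for gene expression, and neither it, section 3.3 nor the SAP gives an analysis that can meet it. The gap is more than missing detail, because the contrast that is written cannot separate modifiers from prognostic genes whichever way disease group is read.

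The size depends on assumptions. With disease group taken as LCOS and 300 to 1000 sampled children, a prognostic gene of OR 1.5 per SD is flagged in about 84 to 100% of runs, against about 3 to 6% for an interaction test. The number sampled, the gene effects and, in Setting A, the event rates are assumed; only the pilot LCOS rates come from the protocol. The absence of any arm term does not depend on them.

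The consequence is confined to an exploratory sub-study on optional samples. Ventilator-free days, the clinical secondary outcomes and the interim decisions are untouched.

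**What to change.** In the gene-expression paragraph of protocol 7.3, or in a separate analysis plan for the biobank fixed before the transcriptomic data are analysed:

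- Define 'disease groups' and state the false-discovery cut-off.
- Keep the edgeR, WGCNA and signature analyses, and say that they address prognosis.
- For the response aim, test the interaction of pre-bypass expression, or module eigengene, with randomised arm on ventilator-free days and on the LCOS/ECLS/death composite. Adjust for age group, physiology and site, with Benjamini-Hochberg control across markers. The SAP's subgroup section already gives the model form.
- Leave the PICU-admission RNA sample out of the modifier test, because it follows NO exposure. It can still show what NO does to expression.
- Call only markers with an interaction markers of response.

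If the interaction analysis is not wanted, limit the stated gene-expression aim to prognosis.

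The cost is wording and one further model per marker and outcome on samples and data already planned. The downside is power: interaction tests generally have less of it, so the list of response markers will be shorter and may be empty.

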#### 7.4 HEALTH ECONOMIC EVALUATION

**Economic Evaluation.** A with-in trial economic evaluation will be undertaken from the health system perspective to compare the cost of providing NO to that of usual care. Resources to be measured and costed will include the number of length of stay (in PICU and/or non-intensive stay), and the length of ECLS treatment. Costs will be assigned by the hospital cost centre or standard national sources (e.g. Independent Hospital Pricing Authority). Both parametric (e.g. ANCOVA) and non-parametric bootstrapping techniques [37] will be employed to compare mean difference in the costs between groups, and to estimate a confidence interval around the mean. It is anticipated that NO intervention will be cost saving to the health system. The cost comparison will inform recommendations on adopting NO in standard CPB practice.

#### 7.5 NEURODEVELOPMENTAL EVALUATION

The consent of study participants specifically mentions that families will get contacted a year post intervention for follow-up.

Patients will be followed up at all sites at 12 months post intervention (range of 10 to 15 months post intervention is recommended). The 1-year follow-up will be based on surveys which parents can attend/complete from home (less than 20 mins time commitment required) and will assess Quality of Life (pedsQL), neurodevelopment (Ages and Stages Questionnaire), and socioeconomic status.

In order to obtain more granular information on neurodevelopmental outcomes, families will be offered a full neurodevelopmental assessment as well. This will be restricted to sites where funding and local resources and expertise allow, and coordinated with the local practice of follow-up to reduce time commitment for families.

Neurodevelopmental assessment will be performed by an experienced paediatric neuropsychologist, using the Bayley-III SE, at 12-month post intervention. The Bayley-III is recognised internationally as one of the most comprehensive tools to assess children from as young as one month old and represents the most widely used developmental assessment tool during pre-school which is widely

used in neonatal follow-up across the world. Bayley-III identifies infant and toddler strengths and competencies, as well as their weakness. It also provides a valid and reliable measure of a child's abilities, in addition to giving comparison data for children with high incidence clinical diagnoses. Descriptive statistics will be utilised to report on the baseline characteristics of the study cohort and each subgroup. Proportion of children with a neurodevelopmental deficit will be analysed using a Chi-square/Fisher exact tests. Analysis of association includes both comparisons of measurements and proportions, using confidence intervals of differences as the major method of presentation where possible, otherwise standard techniques such as Mann-Whitney U tests, t-tests and chi-squared tests will be utilised. The raw score for Bayley-III is standardized to a mean of 100 with an SD of 15 (range, 50-150). The standardized score is also classified into the categories of accelerated performance (>115), within normal limits (85-115), and delayed performance (<85). Statistical significance will be set at the 0.05 level for the secondary outcomes. It is anticipated the neurodevelopmental outcomes at 12 months will provide data for feasibility, sample size calculation and design of long term neurodevelopmental assessments within the study towards school age outcomes.

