## **Randomisation**

Randomisation is conducted online through the purpose-built REDCap electronic data capture tool hosted at The University of Queensland (14, 15); the randomisation module can only be accessed by the central study coordinator and the site perfusionist, and only after a patient has been screened, is deemed to have met eligibility criteria and has provided informed consent. A randomisation sequence using variable block randomisation with a 1:1 ratio was generated and loaded into REDCap prior to screening of the first patient. Randomisation is stratified on age (<six weeks, ≥six weeks), cardiac physiology (univentricular, biventricular) and study site. The precise time of randomisation occurs variably prior to starting CPB dependent on site logistics, and the intervention begins with start of CPB.

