### *Secondary outcome measures*

For binary outcome measures (e.g. LCOS), logistic regression analyses will be used including age group and physiology as fixed effects, and site as a random effect, with unadjusted and adjusted odds ratios (ORs) and 95% CIs reported (Table 3). Survival outcomes (length of PICU stay, length of hospital stay) will be visually presented using a Kaplan-Meier plot and a Cox proportional hazard model will be used to assess differences between treatment groups with

treatment group and stratification variables as fixed effects and site as a random effect (i.e. utilising a shared frailty model). The hazard ratio and 95% CI will be presented as an estimate of treatment effect. Continuous outcomes (e.g. PELOD-2, duration of renal replacement therapy) will be analysed using linear regression adjusting for age group and physiology as fixed effects, and site as a random effect, with mean difference and 95% CI reported. If the residuals demonstrate non-normality, quantile regression will instead be used in the same manner as for the primary outcome. Key assumptions of the models will be tested and reported on (for logistic regression: specification, goodness-of-fit, absence of multicollinearity and absence of influential observations; for survival analysis: proportionality assumption, goodness-of-fit; for linear regression: specification, distribution of residuals, homoscedasticity, absence of multicollinearity, linearity).

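### The 12-month neurodevelopmental comparisons are planned with unadjusted tests that ignore the randomisation strata, at a modest and avoidable cost in power

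*Combined protocol and SAP*

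**What the plan says.** Protocol section 7.5 is the only text in the documents that sets an analysis method for the 12-month neurodevelopmental outcomes. It gives one test for one outcome: "Proportion of children with a neurodevelopmental deficit will be analysed using a Chi-square/Fisher exact tests". For the rest it says "Analysis of association includes both comparisons of measurements and proportions, using confidence intervals of differences as the major method of presentation where possible", and then "otherwise standard techniques such as Mann-Whitney U tests, t-tests and chi-squared tests will be utilised". The significance level is 0.05. The standardised Bayley-III score (mean 100, SD 15) is additionally banded at 85 and 115. The word deficit is not defined, and 7.5 does not say whether the score or the proportion is the main analysis. The Bayley-III assessment is "restricted to sites where funding and local resources and expertise allow", while the parent questionnaires go to all sites.

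Randomisation is stratified by age group, "cardiac physiology (univentricular, biventricular) and study site" (SAP, Randomisation; the same factors appear in protocol section 6.2). For 28-day binary outcomes the SAP says "logistic regression analyses will be used including age group and physiology as fixed effects", with site as a random effect, and it adjusts the primary, time-to-event and continuous outcomes for the same factors. The SAP's statistical analysis principles limit it to 28 days and leave outcomes at 12 months and later to separate presentation.

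**The concern.** A trial that stratifies its randomisation would normally carry the strata into the analysis. Stratification balances the arms on these factors and so reduces the true variability of the treatment difference. An unadjusted test still charges for that variability: its standard error is too large and it rejects too seldom. The protocol itself expects the factors to matter. Section 6.2 describes cardiac physiology as a major driver of outcome and the youngest infants as the highest surgical risk, and section 2.1 says infants and young children carry the highest risk of long-term neurological sequelae.

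At stake is the precision of an arm comparison that the protocol treats as meaningful. Section 3.3 lists neurodevelopmental follow-up, and its relationship to the intervention, among the pre-planned analyses. Section 5.1.2 justifies keeping the same allocation at later operations by a possible effect on long-term neurodevelopment. Bayley-III data come from only some sites, so there is reason not to waste information.

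**Working it through.** **Plan's own figure.** Section 7.5 gives no sample size or power, so there is none to reproduce. The only sample size in the documents, 1,320, is for ventilator-free days. It reproduces closely: 526 per arm for 0.2 SD at 90% power and two-sided 5%, and 526 × 1.10 × 1.15 = 665 per arm, 1,331 in total. It does not bear on this point.

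**Step 1: does any other text supply the adjustment?** Section 7.5 names no stratum, site or covariate. Protocol section 11.1 is equally generic. The SAP's adjusted models cover outcomes to 28 days. So it does not.

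**Step 2: cost of ignoring the strata in a comparison of scores.** Inputs: two-sided 5% (1.960; section 7.5 does not state sidedness, so this is assumed), 80% power for an adjusted analysis as the reference (0.842), and R², the share of score variance explained by the strata. The documents give no R², so it is an assumption, shown as a range.

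With n children per arm, score variance σ² and arms balanced within strata:

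- true variance of the difference in means = (1 − R²) × 2σ²/n
- variance used by the unadjusted test = 2σ²/n
- actual type I error = 2[1 − Φ(1.960/√(1 − R²))]
- unadjusted power = Φ(1.960 + 0.842 − 1.960/√(1 − R²))

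| Assumed R² | 1.960/√(1 − R²) | Type I error | Power (adjusted = 80%) |
|---|---|---|---|
| 0.05 | 2.011 | 0.044 | 78.5% |
| 0.10 | 2.066 | 0.039 | 76.9% |
| 0.20 | 2.191 | 0.028 | 72.9% |

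The error is on the conservative side throughout. The figures suppose that balance within strata survives among the children actually assessed at 12 months.

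**Step 3: cost of a cut at <85, if the comparison rested on it alone.** For a normal score with SD 15, the efficiency of a cut at 85 relative to a comparison of means is φ(c)²/[p(1 − p)], where c = (85 − cohort mean)/15 and p = Φ(c). The mean of 100 in section 7.5 is the test's standardisation value. No cohort mean is given, so lower values are assumptions.

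| Assumed cohort mean | Proportion <85 | Efficiency | Loss |
|---|---|---|---|
| 100 | 15.9% | 0.439 | 56% |
| 95 | 25.3% | 0.541 | 46% |
| 90 | 36.9% | 0.611 | 39% |
| 85 | 50.0% | 0.637 | 36% |

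The loss exceeds half only if the cohort mean is above about 97. In numbers of children, a 5-point difference at 80% power needs 142 per arm on the score. On the cut it needs 377 per arm at a mean of 100 (15.9% against 9.1%) and 226 at a mean of 85 (50.0% against 36.9%).

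**The case against.** The defence is substantial. The SAP openly stops at 28 days and promises the long-term outcomes separately. Protocol section 11.1 used much the same generic wording for the 28-day outcomes, and the SAP later refined it, so a follow-up SAP could do the same here. The list of tests in 7.5 is open-ended. The SAP itself reports unadjusted results beside the adjusted ones. The stated purpose of the 12-month data is feasibility and the design of later assessments, and the SAP regards secondary results as exploratory. The unadjusted tests do not inflate type I error, and they do not bias the standard deviations or proportions that would be used to size a school-age study.

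All of this limits the size of the point, but none of it supplies the missing adjustment. Until a follow-up SAP exists, 7.5 is the governing text, and it carries a 0.05 threshold.

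Two stronger readings are tempting, and the documents do not support them.

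- A reader might infer that the plan discards over half the information in the Bayley-III score. But 7.5 plans comparisons of measurements as well as proportions and makes the banding additional to the score; t and Mann-Whitney tests on the score lose nothing to a cut. The loss in Step 3 applies only to the proportion. It also requires reading deficit as <85, which is an inference, and it passes half only at a cohort mean above about 97.
- A reader might infer that children who died are left out of the comparison. Section 7.5 is silent on deaths, and silence does not establish exclusion. Mortality is already a separate secondary outcome. Ranking death as the worst developmental result would be a choice of estimand, not a correction.

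**Conclusion.** The point holds and is modest. As written, the 12-month neurodevelopmental comparisons use unadjusted tests despite stratified randomisation, and no other text in the documents corrects this. For the score comparisons, if the strata explain 5-20% of variance, type I error is about 0.044-0.028 instead of 0.05, and power is about 79-73% instead of 80%. That range is an assumption; the protocol says only that the strata are prognostic. These figures apply to linear models. For the deficit proportion, logistic adjustment changes the odds ratio being estimated to one within strata and does not narrow its standard error, so the same gain should not be claimed there.

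A secondary gap is that deficit has no stated cut-off and no main analysis is named. This leaves open whether the weight falls on the full score or on a less efficient proportion.

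**What to change.** In section 7.5, or in the follow-up SAP before the 12-month data are compared by arm:

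- Name the continuous Bayley-III score, and the questionnaire scores, as the main comparison. Use linear regression on arm with age group, physiology and site, and report the mean difference and 95% confidence interval.
- Define deficit by stating its cut-off. Report the proportion as supportive, using the strata-adjusted logistic model the SAP already applies to 28-day binary outcomes.

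The cost is wording only. The strata are recorded at randomisation, and section 7.6 already has them verified for every enrolled patient, so no new data are needed.
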